## Abstract

**Background:**

When depression accompanies diabetes, it complicates treatment, portends worse outcomes and increases health care costs. A collaborative care case-management model, previously tested in an urban managed care organization in the US, achieved significant reduction of depressive symptoms, improved diabetes disease control and patient-reported outcomes, and saved money. While impressive, these findings need to be replicated and extended to other healthcare settings. Our objective is to comprehensively evaluate a collaborative care model for comorbid depression and type 2 diabetes within a Canadian primary care setting.

**Methods/design:**

We initiated the TeamCare model in four Primary Care Networks in Northern Alberta. The intervention involves a nurse care manager guiding patient-centered care with family physicians and consultant physician specialists to monitor progress and develop tailored care plans. Patients eligible for the intervention will be identified using the Patient Health Questionnaire-9 as a screen for depressive symptoms. Care managers will then guide patients through three phases: 1) improving depressive symptoms, 2) improving blood glucose, blood pressure and cholesterol, and 3) improving lifestyle behaviors. We will employ the RE-AIM framework for a comprehensive and mixed-methods approach to our evaluation. Effectiveness will be assessed using a controlled “on-off” trial design, whereby eligible patients would be alternately enrolled in the TeamCare intervention or usual care on a monthly basis. All patients will be assessed at baseline, 6 and 12 months. Our primary analyses will be based on changes in two outcomes: depressive symptoms, and a multivariable, scaled marginal model for the combined outcome of global disease control (i.e., A1c, systolic blood pressure, LDL cholesterol). Our planned enrolment of 168 patients will provide greater than 80% power to observe clinically important improvements in all measured outcomes. Direct costing of all intervention components and measurement of all health care utilization using linked administrative databases will be used to determine the cost-effectiveness of the intervention relative to usual care.

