This concept was recently proven in a pair of randomized trials investigating the efficacy of a case-management collaborative care model for patients with diabetes and depression in the primary care setting of Group Health Cooperative in Washington State [28,29]. In the first trial, a case-management approach proved effective in reducing depressive symptoms, but did not result in improved glycemic control [28]. In the second study, the case-managed collaborative care model was expanded in scope, aimed at achieving improvements of depressive symptoms and cardio-metabolic markers in individuals with depression and poorly controlled diabetes or heart disease [29]. In both cases, a nurse care manager guided patient-centered care with family physicians and consultant physician specialists. In the second study the intervention initially focused on the treatment of depression, but also aimed at management of diabetes and cardiovascular risk factors (e.g. high blood pressure, elevated lipids, elevated A1c), as well as lifestyle health-related behaviors. The trial involved 214 patients from 151 physicians in 14 primary care clinics. Patients in the intervention group had greater overall 12-month improvement across A1c (difference, 0.58%), LDL cholesterol (difference, 0.2 mmol/L), systolic blood pressure (difference, 5.1 mm Hg), and SCL-20 depression scores (difference, 0.40 points) (P < 0.001). Patients in the intervention group also were more likely to have one or more adjustments of antihypertensive medications (P < 0.001), insulin (P = 0.006), and antidepressant medications (P < 0.001), and they had better quality of life (P < 0.001) and greater satisfaction with care (P < 0.001). Patients in the intervention group had a mean of 10.0 in-person and 10.8 telephone visits with the nurse care manager over the 12-month period. The estimated mean cost per patient for this intervention, including all nurse contacts, specialist physician consultations, and information system support, was $1,224 (USD) in 2009 [29]. However, these intervention costs were offset by savings in total medical costs; over a 24-month period the intervention was associated with approximately $600 cost savings per patient compared to usual primary care [30].

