### Eligibility criteria

Inclusion Criteria:

 · Have type 2 diabetes and under the care of a PCN family physician and be

 · 18 years of age or older and

 · Score > =10 on the PHQ-9 [29,39,40] and

 · Speak English and have adequate hearing to complete telephone interviews and

 · Be willing and able to provide written informed consent to participate

Exclusion Criteria:

 · Severe and/or terminal physical illness (e.g. heart disease, renal failure, cancer, major organ failure) or

 · Serious and/or severe mental or psychiatric illness (e.g. bi-polar disorder or schizophrenia, use of anti-psychotic or mood stabilizer medication, or cared for by a psychiatrist); patients taking anti-depressants or receiving supportive psychotherapy from non-psychiatrists would be eligible or

 · Pregnant or breastfeeding or

 · Live in long-term care facility or

 · Already participating in other clinical trials

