### Data analysis

As the initial focus of the intervention is on the management of depressive symptoms, we have considered the PHQ-9 as a main primary outcome, and will assess changes in PHQ-9 scores over 12-months between groups, adjusting for baseline PHQ-9 score, using a mixed effects multivariate model. For our second primary outcome of improvements in global disease control, we will employ a multivariate model that jointly tests the changes in multiple clinical outcomes, namely A1c, LDL cholesterol and systolic blood pressure [29]. Using the same analytic approach as in the recently published RCT of this intervention, we will apply a scaled marginal model [29,75] to simultaneously compare the change in these continuous outcomes at 12 months, adjusting for the baseline status for each variable. This approach scales the changes in each outcome by its standard errors, and thus the coefficients can be directly interpreted as effect sizes [29]. In either primary outcome analyses, the models will be estimated iteratively and the potential correlations among and between outcomes within individuals will be handled using generalized-estimating equation (GEE) models for each outcome [75].

We will also compare the study arms based on the proportion of subjects who achieved a remission of depression (i.e., PHQ-9 < 10 for 3 consecutive months) and the proportion of patients who achieve a clinically important change in the outcomes (that is, achieving a reduction of 5 points on the PHQ-9 [44] or a 10% or greater improvement over baseline values for A1C, LDL cholesterol and SBP at 12 months) [59,60], using generalized estimating equations and multivariable logistic regression models. This approach will allow us to present and interpret all outcomes in terms of absolute differences and a number-needed-to-treat [76].

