### Sample size and power considerations

We estimate that a minimum total sample size of 120, with 60 in each arm, would provide power of 0.80 to detect a mean difference of 5 points in the PHQ-9 [44], assuming a repeated measures correlation of 0.6, and 2-tailed alpha of 0.05. This sample size also provides more than 80% power (two sided alpha = 0.05) to detect any between-group absolute difference in proportions of 15% or more (e.g., 45% of usual care patients achieve depression remission vs 60% of intervention patients) [29]. Anticipating a 40% attrition rate, we planned to recruit 168 patients in total across our 4 PCN sites. Although the model is implemented in 4 PCN sites, the individual general physicians affiliated with the PCN will carry out the changes in care. While we will include PCN site as a covariate in our analysis, because there are approximately 140 general physicians across these 4 PCN sites, we choose not to further inflate our sample to account for clustering of patients and their outcomes.

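### The abstract's claim of more than 80% power for all measured outcomes is not supported by the sample size section, is false for the section's own proportions example, and has no stated basis for the second primary outcome

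*Protocol article*

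**What the plan says.** The abstract (Methods/design) makes a blanket claim: "Our planned enrolment of 168 patients will provide greater than 80% power to observe clinically important improvements in all measured outcomes".

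The section on sample size and power gives two calculations for a total of 120. The first is that 60 per arm "would provide power of 0.80 to detect a mean difference of 5 points in the PHQ-9", "assuming a repeated measures correlation of 0.6, and 2-tailed alpha of 0.05". The second is more than 80% power to "detect any between-group absolute difference in proportions of 15% or more", illustrated by depression remission in 45% versus 60% of patients. Enrolment is then raised to 168 for an expected 40% attrition.

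The Data analysis section names two primary outcomes. One is PHQ-9. The other is a scaled marginal model that "jointly tests the changes in multiple clinical outcomes, namely A1c, LDL cholesterol and systolic blood pressure", with adjustment for baseline. Separately, the arms are compared on the proportions with at least a 10% improvement in each of the three measures. Missing follow-up is filled by last observation carried forward.

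The only between-group differences for A1c, LDL and blood pressure are in the Background, from the second earlier trial: 0.58%, 0.2 mmol/L and 5.1 mm Hg, without SDs. That trial aimed at "improvements of depressive symptoms and cardio-metabolic markers in individuals with depression and poorly controlled diabetes or heart disease". In the present trial the disease criterion is "Have type 2 diabetes and under the care of a PCN family physician and be", joined to age, a PHQ-9 score of at least 10, language and consent. No A1c, LDL or blood pressure threshold is listed.

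**The concern.** The abstract puts a number on the power for every outcome, while the section meant to support it covers one continuous outcome and one general statement about proportions. The second primary outcome appears in neither. This is not detail left for an analysis plan: the article makes a quantified claim that its own calculations do not reach.

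The stake is how a null result is read. If the joint disease-control test, LDL alone or a responder comparison shows no difference, readers will weigh it against a published power above 80% and may take it as good evidence that the model does not improve that outcome in Canadian primary care. For some of these outcomes the real power is well below that figure, and for the second primary it was never stated.

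**Working it through.** **1. The PHQ-9 figure.** No SD is given, so 120 cannot be reproduced exactly. With a two-sample t-test at two-sided 0.05 and 60 per arm, 80% power needs a standardised difference of 0.516. A 5-point difference therefore implies an SD of the analysed quantity of 5/0.516 = 9.7. With an assumed SD of 6, power is about 99%. This part of the claim is not in dispute here.

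**2. The proportions figure, from the article's own inputs.** Power = Φ[(0.15 − 1.96·SE0)/SE1], where SE0 = √(2·0.525·0.475/n) and SE1 = √((0.45·0.55 + 0.60·0.40)/n).
- n = 60: SE0 = 0.0912, SE1 = 0.0901; (0.15 − 0.1787)/0.0901 = −0.318; power 37.5%.
- n = 84 (all 168): SE0 = 0.0771, SE1 = 0.0762; (0.15 − 0.1510)/0.0762 = −0.013; power 49.5%.
- n = 50 (168 × 0.6 ≈ 101 in total): power 32.2%.

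Reaching 80% needs 173 per arm. At 60 per arm a 15-point difference reaches 80% only when the lower rate is about 2% or less (2% versus 17%: 80.8%). The claim for all outcomes is therefore false without any outside assumption.

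**3. Single components of the second primary.** Inputs: the earlier trial's differences, and the plan's correlation of 0.6, applied here to these measures as well. Baseline adjustment multiplies the SD by √(1 − 0.6²) = 0.8. The difference detectable with 80% power is 0.516 × 0.8 = 0.413 SD at 60 per arm and 0.435 × 0.8 = 0.348 SD at 84. The largest SD that still gives 80% power is the difference divided by that value:

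| | 60 per arm | 84 per arm |
|---|---|---|
| A1c, 0.58% | 1.41 | 1.67 |
| LDL, 0.2 mmol/L | 0.48 | 0.57 |
| SBP, 5.1 mm Hg | 12.4 | 14.7 |

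The SDs are assumptions, because the article gives none. At 60 per arm, power is 59-91% for A1c (SD 1.8-1.2), 27-49% for LDL (SD 1.0-0.7) and 41-70% for SBP (SD 20-14). At 84 per arm, LDL has 36-63%.

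**4. The joint model.** It is approximated as a common standardised effect, the mean of the three differences each divided by its SD. The standard error is reduced by √((1 + 2r)/3), where r is the between-outcome correlation. For SDs of 1.5/0.85/17 the mean is (0.387 + 0.235 + 0.300)/3 = 0.307; for 1.2/0.7/14 it is 0.378 and for 1.8/1.0/20 it is 0.259. With r = 0 to 0.2 and the full differences:
- 60 per arm: 73% to 99%; mid case (middle SDs, r = 0.1) 91%.
- 84 per arm: 86% to nearly 100%; mid case about 97%.

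If the effect were only 0.7 or 0.5 of the earlier one (illustrative factors), the mid case falls to 64% or 38% at 60 per arm and to 78% or 50% at 84.

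The common effect detectable with 80% power at 60 per arm and r = 0.1 is 0.413 × √(1.2/3) = 0.26 SD.

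These calculations use 0.05 for each primary outcome and ignore clustering. The 84-per-arm figures count all 168 as fully informative. Carrying last observations forward for those lost would tend to shrink a real difference, so these figures are favourable.

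**The case against.** A reader might say that only depression outcomes were sized. That is too strong. The proportions statement is general, remission is only its example, and it would also cover the comparisons of patients with a 10% improvement in A1c, LDL or blood pressure. The abstract's wording about clinically important improvements may well refer to these. This objection stands, but it does not rescue the abstract, because the proportions statement is itself wrong (step 2).

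A reader might also infer that the second primary is underpowered and that a null result is likely, since patients need not be poorly controlled at entry and those already at target have little to gain. The article does not support that conclusion, for three reasons.
- It gives no SDs, between-outcome correlation or fraction above target. With the full earlier differences, power exceeds 80% over much of the assumed range.
- Scaling the earlier effect by the fraction above target may count dilution twice. Patients with poorly controlled diabetes or heart disease need not have been above target on all three measures, so the earlier differences may already average over some who were at target.
- Even at 0.7 of the effect, the mid case has 64% power at 60 per arm, so a null would be the less likely result.

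Finally, power for LDL alone is not power for the joint test. That is correct. The LDL figure counts against a claim about all measured outcomes, not against the joint model.

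**Conclusion.** The abstract's power statement is wrong as written. On the article's own inputs it fails for a 45% versus 60% difference: 37.5% power at 60 per arm and 49.5% with all 168. On assumed LDL SDs of 0.7-1.0 mmol/L it also fails for the earlier trial's LDL difference at either size.

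For the second primary outcome, the supportable conclusion is that power has not been established, not that it is inadequate. It may be above or below 80%, depending on the SDs, the between-outcome correlation and how much of the earlier effect recurs in patients enrolled without a disease-control threshold. The PHQ-9 statement is the only part that the abstract can reasonably keep.

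**What to change.** In the abstract, limit the power statement to the 5-point PHQ-9 difference. The 15-point proportions sentence should not be used to support anything wider; at 60 per arm it needs correcting or withdrawing.

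In the sample size section, add the effect detectable with 80% power for the second primary at the planned size: a common effect of about 0.26 SD at 60 per arm, with baseline correlation 0.6 and between-outcome correlation 0.1 stated as assumptions. Add that power against the earlier trial's differences depends on the SDs and on how well controlled the enrolled patients are.

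These are wording changes. Enrolment and the primary analysis are unaffected, and the only downside is a less favourable stated power.

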**Discussion:**

Our comprehensive evaluation will generate evidence to reliability, effectiveness and sustainability of this collaborative care model for patients with chronic diseases and depression.

**Trials registration:**

Clintrials.gov Identifier: NCT01328639

## Background

Depression is one of the most common co morbidities in people with diabetes, present in 15-30% of patients with type 2 diabetes [1], at rates that are 30-40% higher than the general population [1,2]. Despite this, less than 50% of patients are recognized as having depression within the health care system [1,2]. Depression itself is a risk factor for the development of type 2 diabetes [3-5], and it is associated with adverse diabetes-related outcomes [6-9]. For example, comorbid depressive disorders in people with diabetes are associated with poorer self-care behaviors [10,11] worse glycemic control, higher risk of microvascular and microvascular diabetes-related complications [8-11], decreased quality of life and psychological well-being [2,12,13], and substantially higher health care costs [6,14,15]. The implications of untreated depression on long-term morbidity and mortality are even more significant when one considers that depression tends to be a recurrent condition, with 79% of diabetic patients with depression relapsing over a 5-year period with an average of 4 or more episodes [13,16]. In turn, diabetes may worsen the course of depression [4,16]. In fact, having one or more chronic medical condition, such as diabetes, increases the likelihood of developing a major depressive episode [17].

Although the majority of individuals with diabetes and depression are treated in primary care settings [18], only a minority of these individuals receive adequate treatment for depression [6,10,18]. Indeed, despite its high prevalence, less than one-half of all patients with depression are diagnosed or adequately treated [19,20]. Even primary care patients with established and treated depression receive only 48% of recommended management with both medication and psychotherapy [20]. It is also true that these rates of adequate treatment are much lower for those with diabetes, given that up to one-half of these patients have undiagnosed depression [1,19,20]. Depression has also been reported to be an important barrier to enhancing self-management, quality of care and outcomes in individuals with diabetes in primary care settings [18,21,22].

Traditional approaches to improving primary care of patients with complex comorbid chronic illnesses typically involves “carve-out” disease management programs, that is, delivering care for each condition, one disease at a time. Such single-disease management programs have been shown to be effective in improving control of conditions such as heart failure [23], diabetes [24,25], and depression [26]. However, a recent systematic review and meta-analysis of interventions for depressive disorders in patients with diabetes concluded that pharmacologic and collaborative care interventions were primarily aimed at and succeeded in the reduction of depressive symptoms, but, in general, had no effect on glycemic control [27]. It was suggested that individuals with comorbid physical and psychological problems require a far more integrated approach of care that targets such conditions collectively, and that management of these comorbid conditions should not be done separately [27].

This concept was recently proven in a pair of randomized trials investigating the efficacy of a case-management collaborative care model for patients with diabetes and depression in the primary care setting of Group Health Cooperative in Washington State [28,29]. In the first trial, a case-management approach proved effective in reducing depressive symptoms, but did not result in improved glycemic control [28]. In the second study, the case-managed collaborative care model was expanded in scope, aimed at achieving improvements of depressive symptoms and cardio-metabolic markers in individuals with depression and poorly controlled diabetes or heart disease [29]. In both cases, a nurse care manager guided patient-centered care with family physicians and consultant physician specialists. In the second study the intervention initially focused on the treatment of depression, but also aimed at management of diabetes and cardiovascular risk factors (e.g. high blood pressure, elevated lipids, elevated A1c), as well as lifestyle health-related behaviors. The trial involved 214 patients from 151 physicians in 14 primary care clinics. Patients in the intervention group had greater overall 12-month improvement across A1c (difference, 0.58%), LDL cholesterol (difference, 0.2 mmol/L), systolic blood pressure (difference, 5.1 mm Hg), and SCL-20 depression scores (difference, 0.40 points) (P < 0.001). Patients in the intervention group also were more likely to have one or more adjustments of antihypertensive medications (P < 0.001), insulin (P = 0.006), and antidepressant medications (P < 0.001), and they had better quality of life (P < 0.001) and greater satisfaction with care (P < 0.001). Patients in the intervention group had a mean of 10.0 in-person and 10.8 telephone visits with the nurse care manager over the 12-month period. The estimated mean cost per patient for this intervention, including all nurse contacts, specialist physician consultations, and information system support, was $1,224 (USD) in 2009 [29]. However, these intervention costs were offset by savings in total medical costs; over a 24-month period the intervention was associated with approximately $600 cost savings per patient compared to usual primary care [30].

While impressive, these findings need to be replicated and extended to other healthcare settings before the intervention model can be widely adopted or recommended. We took the previous randomized controlled trials as evidence of the efficacy of this case-managed collaborative model of care [28,29]. We therefore proposed a pragmatic approach in the implementation and evaluation of the collaborative care intervention in Primary Care Networks (TeamCare-PCN), and will employ a mixed-methods approach, based on the RE-AIM framework [31]. The RE-AIM framework examines five dimensions: Reach into target populations; Effectiveness; Adoption by target settings, institutions, and staff; Implementation, including consistency and cost of delivery; and Maintenance of effects in both individuals and settings over time. Thus, while a major focus of our protocol is on effectiveness, based on changes in clinical outcomes, applying the complete RE-AIM framework will allow us to determine the broader impact and transferability of the TEAM care model in the Alberta context.

## Methods

### Overall study design

We will evaluate the effectiveness (i.e., the “E” in RE-AIM) of the TeamCare-PCN intervention using a controlled pragmatic trial design. We have implemented a variant of a practical design referred to as “cohort multiple RCT” (Figure 1) [32]. Patients with type 2 diabetes registered at PCNs will be invited to participate in an ongoing, annual survey as part of a larger Alberta’s Caring for Diabetes (ABCD) Cohort Study. Initial contact with cohort participants includes the administration of the Patient Health Questionnaire, a brief depression screening survey, and if positive for depressive symptoms, respondents will be invited to participate in the TeamCare-PCN study. We will allocate eligible participants to the intervention and usual care arms using an “on-off” time series (Figure 1); all participants will be assessed at baseline, 6 and 12 months.

